In 2020, because of a lack of evidence of their effectiveness, the Medical Technology Product Council in Sweden recommended that weighted blankets for sleep problems should only be prescribed in research studies. This recommendation was then included in the updated treatment guidelines published by the Swedish National Board of Health and Welfare in 2024 [26]. During the same period, our research group conducted a randomized controlled trial in which weighted blankets were compared with lighter control blankets in children with ADHD and sleep problems [27, 28]. Sleep was evaluated both objectively and subjectively by sleep actigraphy, questionnaires, and interviews [27, 29, 30]. Weighted blankets were found to increase total sleep time (mean difference 7.72 min) and sleep efficiency (mean difference 0.82%) and reduce nightly awakenings (mean difference − 2.79 min) and perceived sleep problems compared with the lighter control blankets. They were particularly effective for children 11–14 years of age with the inattentive subtype of ADHD. Results from sleep actigraphy did not support any changes in sleep onset [27]. The children experienced that the weighted blanket required adjustment to individual needs and preferences and adaptation to the environment, improved their ability to regulate worry and anxiety, changed sleep patterns, and promoted functioning in everyday life [29]. Parents experienced improved sleep routines, faster sleep onset, fewer awakenings, and increased well-being in their children, which in turn improved the children’s ability to manage school, leisure activities, and family life [30].

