The studies by our research group have established knowledge about the development, feasibility, and evaluation of a weighted blanket sleep intervention for children with ADHD and sleep problems. The final phase, implementation, focuses on how the intervention works in clinical practice [31] to ensure that it is feasible, (cost-)effective, transferable, and scalable. The aim of this study protocol is to describe a research project evaluating the real-world effectiveness and implementation of a weighted blanket intervention and standard melatonin treatment in routine clinical practice for children with ADHD and sleep problems. The project focuses on: (1) effectiveness, including changes in sleep-related outcomes, treatment adherence, health-related outcomes, and resource utilization within and across the initial treatment arms during the first 12 months after inclusion, (2) longer-term patterns of treatment use, adherence, treatment changes, sleep, health-related outcomes, and resource utilization during the annual follow-ups, and (3) barriers and facilitators in implementation in routine clinical practice. We hypothesize that the two initial treatment arms will show different patterns of change in sleep-related outcomes during the first 12 months, but that both groups will improve according to the CSHQ total score. Changes in the standard melatonin treatment arm are expected to primarily concern sleep onset, whereas changes in the weighted blanket intervention arm are expected to concern other aspects of sleep, including total sleep time, nightly awakenings, and perceived sleep quality. We further hypothesize that approximately half of the children starting with a weighted blanket will continue using it at the one-year follow-up. The annual follow-ups will be used to describe longer-term patterns of continued use, discontinuation, switching between treatments, and combined use of weighted blankets and melatonin.

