### Participants and recruitment

Children aged 6–14 who are diagnosed with ADHD (according to the Diagnostic and Statistical Manual of Mental Disorders [DSM], Fifth Edition) [34], screen positive for sleep problems, and are patients at the ADHD unit at CAMHS in the south-west of Sweden are eligible for inclusion in the research project. Children with presumed uncomplicated ADHD are triaged to the ADHD unit, whereas children with significant comorbidity or complex psychosocial needs requiring more intensive care are referred to regular CAMHS outpatient care and are not eligible for inclusion [35]. Approximately 350 children with presumed uncomplicated ADHD are seen annually at the ADHD unit, and based on clinical estimates, approximately half of them, about 175 children per year, are expected to screen positive for sleep problems and therefore be potentially eligible for the study. Children, and one of their parents, will be asked to participate in the research project. At inclusion, participants will enter one of two initial treatment arms based on family preference and clinical decision-making: a weighted blanket intervention or standard treatment with melatonin. Recruitment of child-parent dyads is expected to continue until approximately 150 children have been enrolled in each of the weighted blanket intervention and standard melatonin treatment groups.

When families first seek treatment for their child at CAMHS, they have a short telephone interview as part of a structured triage. After triage, the children see a physician for assessment and care planning. If applicable, ADHD medication is also prescribed. At this visit, children and parents receive verbal and written information about the research project and are given a sleep problems screening form to fill out and bring to the follow-up visit.

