##### ADHD-related symptoms

###### The swanson, nolan, and pelham scale – parent-reported version (SNAP-IV parent)

The Swanson, Nolan, and Pelham Scale – parent-reported version (SNAP-IV parent) [59, 60] assesses children’s ADHD symptoms and Oppositional Defiant Disorder (ODD) symptoms. The questionnaire includes 30 questions rated by the parent on a four-point Likert scale (0–3 points). Attention deficit is covered by nine items and scored from 0 to 27 points. Hyperactivity and impulsivity are combined, covered by six items and three items respectively, and scored from 0 to 27 points. ODD is covered by eight items and scored from 0 to 24 points. A higher score reflects greater severity of symptoms. The additional four items are supplementary to ADHD (two items) and ODD (two items) and will not be included in scoring [59, 60]. SNAP-IV parent demonstrates satisfactory validity and reliability [59, 61].

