### Statistical power

The primary outcome is the CSHQ total score. In the absence of an established minimal clinically important difference for the CSHQ and robust estimates of the expected effect of melatonin on CSHQ scores, the sample size calculation was based on previous publications from the SLEEP project, including the randomized controlled crossover trial and subsequent analyses of the same cohort [27, 74, 75], together with studies of melatonin interventions using the CSHQ [76, 77]. In the SLEEP project, the baseline mean CSHQ total score was approximately 53, with an SD of approximately 8, and an assumed follow-up mean of 47 was used for the weighted blanket intervention. Studies of melatonin interventions have reported improvements of approximately 10 points, corresponding to an assumed follow-up mean of 43, with an SD of 8 [76, 77]. Based on the assumed follow-up means of 47 and 43 and a common SD of 8, the standardized effect size was estimated as Cohen’s d = (47 − 43)/8 = 0.50. With 80% statistical power and a two-sided alpha of 0.05, 64 participants are required per treatment group. Given the uncertainty in the assumptions underlying the sample size calculation, and to allow for expected attrition, switching between treatments, combined use of weighted blankets and melatonin during the first 12 months, and retention of a sufficient sample for longer-term follow-up analyses, we aim to include 150 children per initial treatment arm, for a total of 300 children.

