### Data analysis

#### Quantitative methods

Data analysis will be performed using IBM SPSS Statistics software v.28 or later (IBM Corp., Armonk, NY, USA). Continuous data will be presented as means and standard deviations or medians and interquartile ranges, and categorical data as numbers and percentages. Changes over time in continuous outcomes assessed repeatedly, including the primary sleep outcome, additional sleep-related measures, and health-related outcomes, will be analyzed using repeated-measures analysis of variance (R-ANOVA) or repeated-measures analysis of covariance (R-ANCOVA), as appropriate. Analyses to assess real-world effectiveness within and across the initial treatment arms will include the primary sleep outcome, treatment adherence, health-related outcomes, and resource utilization, using appropriate statistical methods, such as t-tests, chi-squared tests, or analysis of covariance (ANCOVA). When appropriate, age, sex, ADHD medication, and level of ADHD symptoms, will be included as covariates in R-ANCOVA or ANCOVA models. Analyses of long-term follow-up will take into account patterns of treatment use and changes over time, including continued use, discontinuation, switching between treatments, and combined use of weighted blankets and melatonin. Differences in resource utilization will be analyzed through non-parametric analyses of individual data. To address the risk of Type I errors due to multiple comparisons across several outcome measures, Bonferroni corrections will be applied where appropriate.

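### If change over time is tested by R-ANCOVA, the plan should say the covariates are centred; uncentred, the time test concerns a child aged 0 with no ADHD symptoms

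*Protocol article*

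**What the plan says.** The hypotheses at the end of the Background (Protocol article) expect the two arms to follow different patterns over the first 12 months, "but that both groups will improve according to the CSHQ total score". Improvement within each arm is therefore a stated hypothesis.

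Under Quantitative methods, the software is fixed: "Data analysis will be performed using IBM SPSS Statistics software v.28 or later". Repeatedly measured continuous outcomes, the primary sleep outcome among them, "will be analyzed using repeated-measures analysis of variance (R-ANOVA) or repeated-measures analysis of covariance (R-ANCOVA), as appropriate". The covariates are named: "When appropriate, age, sex, ADHD medication, and level of ADHD symptoms, will be included as covariates in R-ANCOVA or ANCOVA models". Nothing is said about their coding or centring, or about which line of the output decides whether an arm improved. The same section also lists t-tests and ANCOVA among the methods for effectiveness inside each arm and between arms.

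Participants and recruitment limits entry: "Children aged 6–14 who are diagnosed with ADHD". Symptom level is measured by SNAP-IV: "Attention deficit is covered by nine items and scored from 0 to 27 points", with a second 0–27 scale for hyperactivity and impulsivity.

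**The concern.** In a repeated-measures model with covariates, the within-child time effect is the intercept of the regression of each time contrast on those covariates. With covariates on their recorded scale, that intercept is the expected change when every covariate equals zero: age 0, symptom score 0, and the zero codes for sex and medication. Age 0 is outside the entry range, and a symptom score of 0 is not plausible in diagnosed ADHD. The hypothesis concerns the mean change of the enrolled children, so the test and the hypothesis would refer to different quantities.

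Taken as baseline values, these covariates are constant within a child. They remove no confounding from within-arm change and only move the point at which change is tested. The result could be a non-significant time effect in an arm that clearly improved or, if change depends on age, a significant one in an arm whose mean change is zero. The same would apply to every repeated continuous outcome analysed this way.

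**Working it through.** **The plan's own figure.** Statistical power gives a between-arm difference of 47 − 43 = 4 with SD 8, so d = 0.50. The t-test solution at 80% power and two-sided alpha 0.05 is 63.77, so 64 per group (63 by normal approximation). The stated 64 reproduces. It rests on a between-arm comparison, so the present point does not touch it.

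**Inputs from the document.** "the baseline mean CSHQ total score was approximately 53, with an SD of approximately 8, and an assumed follow-up mean of 47 was used", which gives a 6-point improvement for the blanket arm. The assumed melatonin follow-up mean is 43, a 10-point improvement. There are five assessments in the first year (baseline, 1, 3, 6 and 12 months) and 150 children per arm.

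**Assumptions not in the document.** Age mean 10, SD 2.5; 33% in the sex category coded 1 (SD 0.47); 70% on ADHD medication (SD 0.458); symptom score mean 32, SD 10 on 0–54; covariates mutually independent; within-child correlation ρ of 0.3, 0.5 or 0.7; improvement present from month 1 and sustained; no missing data. Simulations with a second covariate set (age uniform from 6 to under 15, symptom score mean 30, SD 9) supply the other ends of the ranges below.

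**Step 1: variance multiplier.** With uncentred, independent covariates, the variance of the intercept is multiplied by about 1 + Σ(mean/SD)²:

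1 + (10/2.5)² + (0.33/0.47)² + (0.70/0.458)² + (32/10)² = 1 + 16 + 0.49 + 2.34 + 10.24 ≈ 30.1

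The standard error rises by √30.1 ≈ 5.5. With age as the only covariate the multiplier is 17. With centred covariates it is 1.

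**Step 2: noncentrality, one arm of 150.** Changes of 0, −6, −6, −6, −6 have mean −4.8 and squared deviations 4.8² + 4 × 1.2² = 28.8. Per child, λ = 28.8 / [64(1 − ρ)], which is 0.9 at ρ = 0.5. For 150 children λ = 135 when centred and 135/30.1 ≈ 4.5 when uncentred. The noncentral F with 4 and 4 × 145 = 580 df gives power of about 100% and about 35%.

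**Step 3: power of the time test with uncentred covariates** (formula and simulation, 2,000 to 3,000 replicates per setting):

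| Model | ρ = 0.3 | ρ = 0.5 | ρ = 0.7 |
|---|---|---|---|
| One arm, n = 150, 6 points, four covariates | 25–27% | 31–37% | 52–57% |
| One arm, n = 64, 6 points, four covariates | 13% | 14–16% | 25% |
| One arm, n = 150, 6 points, age only | 44% | 57–60% | 84% |
| Two arms of 150, both 6 points | 51% | 66% | 89% |
| Two arms of 150, 6 and 10 points | 75–77% | 90% | 99% |

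With centred covariates, simulated power was about 100% throughout. The arm-by-time test was identical with and without centring: 82% at 64 per arm and 99.7% at 150 per arm, for ρ = 0.5.

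**Step 4: change that depends on age** (second covariate set, mean age 10.5; slopes assumed; one arm of 150, ρ = 0.5).

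- Mean change −6, improvement growing by 0.5 point per year: change at age 0 is −6 + 0.5 × 10.5 = −0.75. Power is about 5–6%.
- Mean change −6, improvement shrinking by 0.5 point per year: change at age 0 is −6 − 5.25 = −11.25. Power is 87%.
- Mean change 0, slope of 0.5 or 1 point per year: change at age 0 is 5.25 or 10.5 points in absolute value. Rejection is about 25% or 82%, against 4–6% with centring.

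**The case against.** The strongest objection is that the plan never prescribes the faulty test. It does not say covariates are entered as recorded, it brings them in only when appropriate, and it allows R-ANOVA. It also lists t-tests, and a paired t-test of within-arm change does not depend on covariate coding. Coding is commonly left to a full protocol or SAP, neither of which is shown. All of this stands: the problem depends on one permitted branch and one unstated choice. What remains is that the article names the software, the procedure and the covariates, and then leaves open a choice between two tests of different hypotheses.

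A reader might infer that, under this plan, a 6-point improvement would mostly be missed. The document does not support that in general. It holds for a separate one-arm model of 150 with all four covariates uncentred and a correlation of about 0.5 or lower. At 0.7 the change is detected in slightly more than half of trials, and the two-arm model does better still. The two-arm time effect, however, averages over the arms, so it does not show that each arm improved, and it still refers to age 0.

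A reader might also take the earlier trial's finding, "They were particularly effective for children 11–14 years of age with the inattentive subtype of ADHD", as evidence for the age slopes in Step 4. It describes an age-and-subtype subgroup in a comparison with lighter control blankets and gives no CSHQ slope on age. It makes age dependence plausible and does not quantify it.

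**Conclusion.** The point holds as a conditional weakness and is a free improvement, not an error stated in the plan. If R-ANCOVA is run with uncentred covariates, its time main effect does not test the hypothesised mean improvement. The cost can be large: in one arm of 150, power drops from about 100% to somewhere between 25% and 57% over the correlations considered. In a two-arm model with the plan's own changes the loss is smaller, with 75–99% remaining. The test can also reject wrongly if change varies with age.

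The mechanism is algebraic and does not depend on the assumptions. The sizes do: covariate distributions, correlations and age slopes are all assumed. The between-arm (arm-by-time) test, estimated means at the covariate means, R-ANOVA, paired t-tests and the sample size of 64 per group are not affected.

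**What to change.** Add one sentence under Quantitative methods: within-arm change over time is tested by R-ANOVA without covariates, or by R-ANCOVA with every covariate, including the 0/1 codes, centred at its mean in the sample analysed; change is reported as marginal-mean contrasts with confidence intervals at the covariate means. Keep age, sex, ADHD medication and symptom level as covariates for the between-arm comparisons, where they have a purpose because treatment is not randomised.

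The cost is that sentence and one data step to subtract the means. It needs no new data, loses no power and leaves the arm-by-time test unchanged.

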## Methods

### Study design

The research project uses a pragmatic prospective longitudinal cohort design with two initial treatment arms: a weighted blanket intervention and standard melatonin treatment. Treatment selection will be based on family preference and clinical decision-making in routine clinical practice rather than randomization. Child-parent dyads will be followed from baseline to 12 months, with annual long-term follow-ups for an additional nine years. The rationale for the long-term follow-up is to capture children’s development from childhood through adolescence and into young adulthood. The main evaluation of real-world changes in sleep, treatment adherence, health-related outcomes and resource utilization will focus on the first 12 months after inclusion, whereas the annual long-term follow-ups will be exploratory and used to describe longer-term patterns of treatment use, adherence, treatment changes, sleep, health-related outcomes, and resource utilization. Treatment changes may include continued use, discontinuation, switching between treatments, and combined use of weighted blankets and melatonin. The cohort study is combined with a process evaluation and uses a hybrid type 1 effectiveness–implementation approach [32, 33], in which clinical outcomes are the primary focus and implementation outcomes and contextual determinants are explored in parallel. Quantitative, qualitative, and mixed methods will be used.

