#### Sociodemographic variables

Parents will be asked to report their gender (man/woman/prefer not to say), child’s gender (boy/girl/prefer not to say), age, child’s age, civil status (single/spouse or partner), partner age, birth country, birth country of child, birth country of partner, highest educational level achieved (compulsory school/upper secondary school/university or college), partner’s highest educational level achieved, employment status (full time/part time/unemployment/parental leave/studies/sick leave or sickness benefit/other), partner’s employment status, number of siblings, and sibling(s’) age(s). Parents also report child comorbidity (no/yes and diagnoses), child medication (no/yes and type of medicines), child’s need for sleep medication (no/yes), and completion of treatment for sleep problems for the child during the last month (no/yes and type of treatment). An open-ended question enabling additional important information to be communicated is also included.

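### Families and clinicians choose the treatment, yet the across-arm CSHQ comparison may be run unadjusted and baseline CSHQ is not a listed covariate, so the result is open to confounding

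*Protocol article*

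**What the plan says.** **How the arms arise.** Study design states: "Treatment selection will be based on family preference and clinical decision-making in routine clinical practice rather than randomization". Participants and recruitment repeats this.

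**What is compared.** The aims at the end of Background include effectiveness across the two arms over the first 12 months, and the hypothesis is that the arms will change in different ways. Statistical power sizes the study on a difference between arms in follow-up CSHQ: "Based on the assumed follow-up means of 47 and 43 and a common SD of 8". Study design makes the first 12 months the main evaluation and calls only the later annual follow-ups exploratory.

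**How it is analysed.** Quantitative methods assigns change over time in repeated continuous outcomes, including CSHQ, to R-ANOVA or R-ANCOVA. For effectiveness within and between arms it then offers a menu, "using appropriate statistical methods, such as t-tests, chi-squared tests, or analysis of covariance (ANCOVA"), and the outcomes it covers include the primary sleep outcome. Covariates follow in one sentence: "When appropriate, age, sex, ADHD medication, and level of ADHD symptoms, will be included as covariates in R-ANCOVA or ANCOVA models".

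**What is collected but not listed.** Data collection and assessment places the first questionnaires before treatment starts, so baseline CSHQ will exist. Sociodemographic variables also records comorbidity, need for sleep medication, parental education and "completion of treatment for sleep problems for the child during the last month (no/yes and type of treatment"). None of these is in the covariate list. The limitations in the Discussion do not mention confounding by treatment choice.

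**The concern.** In a randomised trial, an unadjusted comparison of follow-up means is unbiased and adjustment is mainly a matter of precision. Here the arm is chosen, so adjustment is what makes the comparison interpretable.

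The article's own account gives reason to expect that choice and sleep profile may be linked. Background expects melatonin to act mainly on sleep onset and the blanket on other aspects of sleep, and says that many parents prefer non-pharmacological treatment. Recruitment takes both newly and previously diagnosed children, so treatment histories will vary.

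If the arms start at different CSHQ levels, part of that difference is carried into the estimated treatment difference. The result could then partly show who chose which treatment. The project aims to inform clinical guidelines, so this bears on how the result will be used.

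**Working it through.** **1. The plan's own sample size.** Inputs from Statistical power: means 47 and 43, SD 8, two-sided alpha 0.05, power 80%. The article concludes: "With 80% statistical power and a two-sided alpha of 0.05, 64 participants are required per treatment group". With d = 4/8 = 0.50, the normal approximation gives 63 per group. The exact two-sample t-test gives 64 (power 0.801 at 64, 0.795 at 63). The stated figure is therefore reproduced, and it is the size for an unadjusted comparison of follow-up means. At 150 per arm the power for d = 0.50 is 0.99, so bias rather than precision is the weak point.

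**2. Assumptions.** The article says that "the baseline mean CSHQ total score was approximately 53, with an SD of approximately 8", but gives no expected baseline difference between arms and no correlation between baseline and follow-up CSHQ. For illustration, take a baseline gap of 2 points (2/8 = 0.25 SD), correlation r from 0.5 to 0.7, and SD 8 at both times. No true effect means that children with the same baseline score have the same expected follow-up score in either arm.

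**3. Raw follow-up comparison.** Bias = r × gap.
- r = 0.5: 0.5 × 2 = 1.0 point, which is 25% of the planned 4 points.
- r = 0.7: 0.7 × 2 = 1.4 points, or 35%.

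Rejection probability = P(|Z + bias/SE| > 1.96), with SE = 8 × √(2/n):

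| Analysed per arm | SE | r = 0.5 | r = 0.6 | r = 0.7 |
|---|---|---|---|---|
| 150 | 0.92 | 0.19 | 0.26 | 0.33 |
| 64 | 1.41 | 0.11 | 0.14 | 0.17 |

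The nominal level is 0.05. A larger sample makes the false-positive rate worse, because the bias stays fixed while the SE shrinks.

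**4. Change score, or time-by-arm contrast in R-ANOVA.** Bias = (r − 1) × gap.
- r = 0.5: −0.5 × 2 = −1.0 point.
- r = 0.7: −0.3 × 2 = −0.6 point.

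Carrying baseline as a time point therefore does not remove the problem under these assumptions. It reverses the sign, through regression to the mean. Two routes that the text leaves open can err in opposite directions on the same data.

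**5. Effect of adjusting for baseline CSHQ.** Under these assumptions this component of bias is removed. The sample needed for 80% power becomes 64 × (1 − r²):
- r = 0.5: 64 × 0.75 = 48 per arm.
- r = 0.6: 64 × 0.64 = 41 per arm.
- r = 0.7: 64 × 0.51 = 33 per arm.

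These figures ignore some loss from correlation between arm and covariates. No larger sample is needed.

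**The case against.** The strongest reply is that Quantitative methods names R-ANOVA or R-ANCOVA first for the primary sleep outcome, which brings in baseline as a time point. The sentence with t-tests is only a list of examples. It spans several outcome types, including adherence, for which a chi-squared test is natural, and a t-test there could be within arm or on change. ANCOVA of a repeated outcome is often understood to include its baseline value. Statistical power uses follow-up means only to size the study. Much of this stands: a reader might infer that the plan commits to a raw t-test on follow-up CSHQ, and it does not. But the text fixes none of the better routes. R-ANOVA carries its own bias (step 4), and the list of covariates leaves baseline CSHQ out.

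A reader might also infer that the arms will differ at baseline and that the result is confounded. The document does not support that as fact. Both arms pass the same sleep screen and come from one unit for presumed uncomplicated ADHD. No section names comorbidity, parental education or recent sleep treatment as reasons for choosing an arm; that they play a part is a reasonable inference.

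The rejection rates at 150 assume that every child enrolled is analysed. The article says "we aim to include 150 children per initial treatment arm, for a total of 300 children" partly to allow for attrition, so the figures at 64 belong beside them.

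Finally, a reader might treat the absence of a full confounder set or a propensity method as an error. An article commonly leaves such detail to the analysis plan, so it is not one.

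**Conclusion.** The point holds in this form: the text permits an unadjusted across-arm CSHQ comparison between self-selected groups, makes covariates conditional without a rule, and leaves baseline CSHQ off the list it gives. The main across-arm result is open to confounding by treatment choice. Its actual size and direction cannot be derived from the document.

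The illustration shows that a modest imbalance matters. A quarter-SD gap is enough to shift a raw follow-up comparison by 25–35% of the planned difference and to raise the false-positive rate to roughly two to three times nominal at 64 per arm, or four to seven times at 150. The result rests on the assumed gap, the assumed correlation, equal SDs and the definition of no effect in step 2. Adjusting for measured variables would not remove confounding by unmeasured ones.

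**What to change.** - For the across-arm CSHQ comparison, and for other continuous outcomes with a pre-treatment value, make the main analysis a model that always includes the baseline value of the outcome, plus age, sex, ADHD medication and SNAP-IV, all as measured at baseline. Remove the conditional wording.
- Add already collected pre-treatment variables that plausibly affect treatment choice, such as recent sleep treatment.
- Keep unadjusted t-tests, chi-squared tests and R-ANOVA as descriptive across-arm analyses.
- For adherence and switching, which have no pre-treatment value, adjust for the pre-treatment covariates only.
- State residual confounding by treatment choice as a limitation.
- A propensity-weighted sensitivity analysis is optional.

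The cost is a few degrees of freedom and a little more analysis work. The variables named here are already collected, and no extra children are needed.
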